##### Baseline measurements

The background questionnaire for the evaluation of the OnVaCT contains socio-demographic items on age, gender, education, living situation, computer experience and online-surfing behaviour. Medical background characteristics (e.g. diagnosis, time since diagnosis, health status, WHO performance status) will be collected from the medical file. In addition, several potential confounding factors will be measured (see also Table 2):
patients’ health literacy;sense of hope;technology acceptance (only in post-test);satisfaction with the tool (only in post-test);quality of life.

##### Outcome measurements

The primary outcome (Table 2) is decisional conflict, i.e. the extent to which patients feel insecure about their decision regarding participation in early phase clinical trials. Secondary outcomes (Table 2) are the communication process (consisting of the extent to which caregivers involve patients in shared decision-making; the discussion of patients’ values and preferences; and the consultation duration) and the actual usage of the OnVaCT (which will be tracked by using Google Analytics).

#### Sample size calculation

The sample size calculation is based on decisional conflict as the primary outcome. Following literature, we assume a mean decisional conflict score of 27 (sd = 12) in the pre-implementation period [7]. To acquire an 80% power to detect an effect size of .30 with an alpha-level of .05 (one-sided), a total sample size of 276 patients is required (138 in the pre-test before the implementation of the OnVaCT and another 138 after the implementation). The three participating hospitals currently see approximately 400–500 new patients a year who consider participation in phase I clinical trials. Based on previous research, we expect a response rate of approximately 40%. We thus need approximately 12 months in the pre-test and another 12 months in the post-test to recruit the required number of patients. We will start the pre-test 18 months before the implementation of the OnVaCT, and if needed, we can spend another 18 months for the post-test. Hence, the inclusion of 276 participants based on the sample size calculation is feasible.

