**Methods:**

In the first part, patients’ values and preferences and medical oncologists’ views hereupon will be explored in interviews and focus groups to build a first prototype OnVaCT using digital communication (serious gaming). Next, we will test feasibility during think aloud sessions, to deliver a ready-to-implement OnVaCT. In the second part, the OnVaCT, with accompanied training module, will be evaluated in a pre-test (12–18 months before implementation) post-test (12–18 months after implementation) study in three major Dutch cancer centres. We will include 276 patients (> 18 years) with advanced cancer for whom standard systemic therapy is no longer available, and who are referred for participation in early phase clinical trials. The first consultation will be recorded to analyse patient-physician communication regarding the discussion of patients’ values and the decision making process. Three weeks afterwards, decisional conflict will be measured.

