##### Evaluation phase (pre-test and post-test)

After giving preliminary oral consent for participation in this study, patients will receive a link to the first questionnaire (T1) via e-mail, which they have to complete before the initial visit with the medical oncologist (T2). The questionnaire starts by asking if the patient gives his/her consent to participate in that particular questionnaire. In the post-test, an additional question will ask whether the patient understands and agrees that data from the OnVaCT will be shared with the oncologist with whom he/she has an appointment. After finishing the first questions, patients participating in the post-test will receive a direct link to the OnVaCT and additional questions regarding technology acceptance and satisfaction with the tool. During both the pre-test and the post-test, written informed consents will be signed and/or collected immediately before the initial visit with the medical oncologist (T2). Subsequently, the initial consultation itself (T2) will be (video- and) audiotaped. Decisional conflict will be measured by means of a final questionnaire 3 weeks after the initial consult with a study medical oncologist (T3).

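### The 276 inclusions equal the number of completed T3 scores needed, so the stated 80% power holds only with no loss before T3

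*Protocol article*

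**What the plan says.** The sample size section of the protocol article (Methods, Part 2) takes the primary outcome as its basis: "we assume a mean decisional conflict score of 27 (sd = 12) in the pre-implementation period". The design target is "To acquire an 80% power to detect an effect size of .30", at one-sided alpha 0.05. The result is "a total sample size of 276 patients is required (138 in the pre-test before the implementation of the OnVaCT and another 138 after" it. The section closes by stating that "the inclusion of 276 participants based on the sample size calculation is feasible", and the Abstract says "We will include 276 patients". The same figure therefore serves as the number required and the number to include.

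On timing, the evaluation-phase procedures state: "Decisional conflict will be measured by means of a final questionnaire 3 weeks after the initial consult". Written consent is an inclusion criterion in Table 1. According to the procedures it is collected immediately before the first consultation (T2); only preliminary oral consent precedes the T1 questionnaire.

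The only rate in the sample size section is a response rate of about 40%. It is applied to 400 to 500 new patients a year to estimate recruitment time. No rate of T3 completion is stated.

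**The concern.** A two-sample calculation returns the number of patients whose outcome enters the comparison. A patient without a T3 questionnaire has no DCS score and contributes nothing to the planned one-sided t-test. If inclusion stops at 276, each missing T3 score takes the analysis below the number that the calculation calls for.

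Some loss is plausible. These patients have advanced cancer with no standard systemic treatment left, and the questionnaire follows three weeks after a consultation about a difficult decision. Some may deteriorate, die, withdraw or not respond.

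At stake is the meaning of a null result, which would be less informative than the stated power implies. Timing also matters: once the tool is implemented, the pre-test group cannot be topped up.

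**Working it through.** **Inputs from the protocol article, sample size section:** effect size 0.30; SD 12, so the difference is 0.30 × 12 = 3.6 points; one-sided alpha 0.05; power 80%; equal groups.

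**Step 1. Reproduce the plan's figure.**
n per period = 2 × (1.645 + 0.842)² / 0.30² = 137.4, rounded up to 138, or 276 in total. This matches the plan exactly. For comparison, a two-sided test would need 175 per period. The stated figure is thus the one-sided number without inflation.

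**Step 2. Exact power at 138 per period.**
Noncentral t with df = 2n − 2 = 274 and noncentrality 0.30 × √(n/2) = 0.30 × √69 = 2.49. Power is 79.98%; with 137 per period it is 79.7%. The number has no slack.

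**Step 3. Power if 138 per period are included and a fraction d lacks a T3 score.**
The loss rates are assumptions, because the documents give none. The number analysed is 138 × (1 − d), rounded. The inclusions needed to keep 138 scores are 138 / (1 − d), rounded up.

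| Assumed T3 loss | Scores per period | Power | Inclusions per period for 138 scores | Total inclusions |
|---|---|---|---|---|
| 0% | 138 | 79.98% | 138 | 276 |
| 5% | 131 | 78.1% | 146 | 292 |
| 10% | 124 | 76.1% | 154 | 308 |
| 15% | 117 | 74.0% | 163 | 326 |
| 20% | 110 | 71.7% | 173 | 346 |

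The difference detectable with 80% power scales as 3.6 × √(138/n). It is 3.8 points at 10% loss (n = 124) and 4.0 points at 20% (n = 110).

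**Step 4. What the planned window can supply.**
Expected participants per year: 0.40 × 400 = 160 to 0.40 × 500 = 200.
- 138 inclusions: 138/200 × 12 = 8.3 months to 138/160 × 12 = 10.4 months.
- 154 inclusions (10% loss): 9.2 to 11.6 months.
- 173 inclusions (20% loss): 10.4 to 13.0 months.
- Loss that a full 12 months could absorb: 1 − 138/160 = 14% to 1 − 138/200 = 31%.

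The window can therefore deliver 138 scores per period under these assumptions, but the target as written does not require it to.

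**The case against.** The strongest counter-argument is the schedule. Recruiting 138 patients should take 8.3 to 10.4 months, yet the plan budgets about 12 per period and allows 18. Twelve months would yield 160 to 200 participants, enough to keep 138 scores at 14 to 31% loss, and no rule says that recruitment stops at 138 inclusions. This stands as evidence that the design can cope. It does not remove the point, because the spare time is nowhere described as an allowance for loss and the stated target remains 276 included.

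A second argument is that an article may leave a retention assumption to the full protocol. That has limited force here, since the article itself prints both the number required and the number to include, and they are identical.

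Two other defences fail. The 40% is a recruitment rate, not a T3 completion rate. The intention-to-treat statement keeps post-test patients who did not use the tool; it does not supply a score for a patient without a T3 questionnaire.

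A reader might also infer more than the documents support:
- *That the 276 are counted at T1.* Nothing says so. With written consent an inclusion criterion and collected just before T2, losses between T1 and T2 need not count against the 276. The interval at risk is about three weeks.
- *That the trial will fall short of 80% power.* That depends on a loss rate which the documents do not give, and on recruitment actually stopping at 276.
- *That the calculation is wrong.* It reproduces exactly.

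**Conclusion.** The point holds as an unstated sample-size assumption, not as an arithmetic error. The 80% power attached to including 276 patients is conditional on every included patient returning a T3 DCS score, and the plan does not say so.

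That no allowance is stated is certain. The size of the consequence is not: it rests on assumed loss between T2 and T3, equal in both periods, with the plan's effect size and SD taken as given. Up to about 5% loss, power stays within two percentage points of 80%, which is of little practical importance. At 10% it is about 76%, and at 20% about 72%. The change is worth making because it is cheap and because the pre-test target cannot be corrected after that period has ended.

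**What to change.** In the sample size section and the Abstract, define 138 per period as patients with a completed T3 DCS, and close each period on that count. This needs no assumed loss rate. For planning, 10 to 20% loss would mean 154 to 173 inclusions per period (308 to 346 in total), reached in about 9 to 13 months at the plan's own rate and so within the 12 to 18 months already foreseen. Set the rule before the pre-test closes.

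If 276 inclusions is kept as the target, state that the 80% power assumes complete T3 data, and show the power over a range of T3 loss labelled as an assumption.

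The cost is a change of wording plus, under the first option, somewhat longer recruitment inside the existing window; under the second, a slightly less favourable stated power. Recruiting to a count of completed scores restores precision only. It does not address bias if patients who miss T3 differ in decisional conflict from those who complete it.

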#### Statistical analysis

All analyses regarding the evaluation of the OnVaCT will be performed in the most recent version of IBM SSPS Statistics. Descriptive statistics and frequency distributions will be generated for the patients’ demographics and medical disease characteristics. For the analysis of the main and secondary outcome measures, an intention-to-treat analysis will be used, thereby including patients who were included in the post-test group (i.e. after the implementation of the OnVaCT with accompanying training) regardless of whether or not they used the OnVaCT.

For the analysis of decisional conflict, a one-sided t-test will be performed between the pre- and post-test measurements. Patient demographics, performance status, health literacy and the level hope may be used as covariates to correct for possible imbalance between the patients from the two study periods (pre-test and post-test) by means of regression analysis. In addition, a mediation analysis will be performed using Structural Equation Modelling (SEM) to calculate the direct effect of the use of the OnVaCT on decisional conflict and to what extent that effect was mediated by communication during the consultation (i.e. the extent to which patients are involved in the decision making process as measured with the adapted Observer OPTION^MCC^ [44]; and the extent to which patient values and preferences are discussed as measured with a codebook we will develop). In the SEM analysis, patient demographics, performance status, health literacy, the sense of hope and the quality of life at baseline may be used as covariates to correct for possible imbalance between the patients from the two study periods (pre- and post-test).

Secondary outcomes, e.g. the total score for the shared decision making process during consultation, the discussion of patients’ values and preferences by patients, relatives and caregivers and the length of the consultation will be compared between the two test periods using two-sided t-tests. Again, the regression analysis may be used to correct for possible differences in patient demographics, performance status, health literacy and hope between the patients from the two study periods (pre- and post-test). Descriptive statistics will be generated for technology acceptance and satisfaction with the tool, which are only measured in the post-test.

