**Discussion:**

This project aims to support the discussion of patient values when considering participation in early phase clinical trials. By including patients before their first appointment with the medical oncologist and recording that consultation, we are able to link decisional conflict to the decision making process, e.g. the communication during consultation. The study faces challenges such as timely including patients within the short period between referral and first consultation. Furthermore, with new treatments being developed rapidly, molecular stratification may affect the patient populations included in the pre-test and post-test periods.

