#### Study design

To evaluate the OnVaCT, we will perform a prospective pre-test post-test multi-centre clinical study to investigate the effect of implementation of the OnVaCT (Fig. 1). In the period between pre-test and post-test the OnVaCT will be implemented. Results on decisional conflict and patient-physician communication measured during the first period of 12–18 months before implementation of the OnVaCT (pre-test) will be compared with the results measured during a second period of 12–18 months after implementation (post-test). In both the pre-test and the post-test data will be collected at three time points:
before the actual visit to the unit for early phase clinical research: registration of baseline characteristics;the initial visit with a medical oncologist regarding early phase clinical studies: measurement of patient-physician communication;three weeks after T2: measurement of decisional conflict.

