It is also important to realize that the pre-test post-test study design could also cause another potential bias in the current project due to the rapidly evolving cancer drug developments, and patients’ perceptions about these (new) drugs as a result. Previous studies have shown multiple shifts in phase I oncology trials over (more than) a decade, including (but not limited to) changes in the distribution of cancer types among patients who participate in these trials [51], patient characteristics and trial designs [52], and decreased toxic death rates [53]. Since the start of the pre-test and the end of the post-test are about 2.5 years apart (see Fig. 1), it may be assumed that shifts in phase I oncology trials are less significant over the inclusion periods of the present study.

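### The primary comparison of two non-randomised periods is an unadjusted t-test; adjustment is optional, its list omits diagnosis and centre, and the plan does not say which result carries the conclusion

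*Protocol article*

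**What the plan says.** The Study design section of Part 2 describes the evaluation thus: "we will perform a prospective pre-test post-test multi-centre clinical study to investigate the effect of implementation of the OnVaCT". Patients in the two periods are different people, and no randomisation, matching or weighting is described. Under Statistical analysis, the primary comparison is set out as follows: "For the analysis of decisional conflict, a one-sided t-test will be performed between the pre- and post-test measurements". The next sentence adds: "Patient demographics, performance status, health literacy and the level hope may be used as covariates to correct for possible imbalance between the patients". The text gives no rule for when the regression applies and does not say whether it replaces the t-test.

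For the SEM mediation analysis the optional list is longer by one item: "the sense of hope and the quality of life at baseline may be used as covariates". The secondary outcomes get two-sided t-tests with the shorter optional list.

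Neither list contains diagnosis or centre. Diagnosis is collected from the medical file (Baseline measurements), and three hospitals take part (Setting). The same Baseline measurements section introduces its list, which includes quality of life, with the words "In addition, several potential confounding factors will be measured".

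On changing patient mix, the Discussion part of the abstract says "molecular stratification may affect the patient populations included in the pre-test and post-test periods". Challenges and limitations cites earlier shifts in phase I oncology, among them "changes in the distribution of cancer types among patients who participate in these trials", and then assumes that such shifts matter less over the roughly 2.5 years of this study.

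**The concern.** In a before-after comparison, any difference in the kind of patient recruited in the two periods is confounded with the tool. Decisional conflict is measured only three weeks after the first consultation, so no baseline score of the outcome is available to absorb such a difference. Regression on baseline characteristics is the one analytic safeguard the article names, yet the article leaves it discretionary and omits the case-mix factor that the authors themselves cite, as well as centre, whose recruitment shares may move between periods.

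Two things are at stake. If the t-test decides, a shift in case mix enters the primary estimate uncorrected. If the regression may take its place, two candidate answers exist, and the text does not say which one supports the conclusion.

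**Working it through.** **Inputs from the Sample size calculation section:** mean 27, SD 12, effect size 0.30 (0.30 × 12 = 3.6 points), one-sided alpha 0.05, power 80%, 138 patients per period, 276 in total.

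**Step 1: reproduce the plan's figure.** n per period = 2 × (1.645 + 0.842)² / 0.30² = 137.4, rounded up to 138, so 276 in total. A two-sided test would need 175 per period. The stated number is therefore right for the unadjusted one-sided t-test, and the sample size and analysis sections agree on that test.

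**Step 2: precision.** SE = √(2/138) = 0.1204 SD = 12 × 0.1204 = 1.44 points. The smallest significant difference is 1.645 × 1.44 = 2.38 points.

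**Step 3: effect of a case-mix difference on the unadjusted test.** The documents give no imbalance, so the sizes below are assumptions. For a bias b (in SD units) towards the tool and no true effect, P(reject) = 1 − Φ(1.645 − b/0.1204). For the same bias against the tool and a true effect of 0.30, power = 1 − Φ(1.645 − (0.30 − b)/0.1204).

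| Assumed bias | Points | Type I error, bias towards the tool | Power, bias against the tool |
|---|---|---|---|
| 0 | 0 | 5% | 80% |
| 0.05 SD | 0.6 | 11% | 67% |
| 0.08 SD | 0.96 | 16% | not computed |
| 0.10 SD | 1.2 | 21% | 51% |
| 0.15 SD | 1.8 | 34% | 34% |

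Two examples of how such values could arise, both assumed:
- A factor correlated 0.4 with the outcome that differs by 0.2 SD between periods gives 0.4 × 0.2 = 0.08 SD, which is 0.08/0.30 = 27% of the target effect.
- A tumour group or centre whose share moves by 20 percentage points and whose mean differs by 6 points gives 0.20 × 6 = 1.2 points, or 0.10 SD.

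**Step 4: what adjustment does to power at 276.** Let R²y be the share of outcome variance explained by the covariates, and R²p the share of period membership they explain. The SE becomes 0.1204 × √((1 − R²y)/(1 − R²p)). Both shares are assumptions.

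| R²y | R²p = 0 | R²p = 0.10 |
|---|---|---|
| 0 | 80% | 76% |
| 0.10 | 84% | 80% |
| 0.20 | 87% | 84% |

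For example, with R²y = 0.10 and R²p = 0: SE = 0.1204 × √0.90 = 0.1142, and Φ(0.30/0.1142 − 1.645) = Φ(0.98) = 84%. The R²p = 0.10 column is the more relevant one if there is measured confounding to remove. Power falls below 80% only when the covariates predict period but hardly predict the outcome.

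**The case against.** The plan is not an unadjusted-only plan. It foresees regression on four groups of covariates expressly to deal with imbalance between periods, and it repeats this for the secondary outcomes and the SEM. A reader might infer that case mix is bound to pass uncorrected into the result. The text does not support that, because the adjusted analysis may be run and may be the one reported. A reader might also infer that the analyst will first look for imbalance and then choose. No such step is stated, only that imbalance is possible.

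Nor is covariate adjustment the only protection. Both periods use the same three hospitals, the same eligibility criteria and the same measurement schedule. The authors also argue that shifts seen elsewhere over a decade or more should be smaller over about 2.5 years. That is reasonable, but it is an assumption, and the abstract still lists a changing population as a challenge.

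The case for quality of life is weaker than for diagnosis. The list of potential confounders that names it also contains technology acceptance and satisfaction with the tool. These are measured only in the post-test and cannot confound a comparison of periods, so that list is not a ready-made adjustment set. One might further argue that the differing covariate lists make the SEM effects irreconcilable with the primary effect. Because both lists are optional and mediation is an additional analysis, no mismatch is actually fixed.

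Finally, this is a condensed article, and details such as how tumour types are grouped belong in an analysis plan that is not shown. That stands for the details. It does not cover the choice of primary test or the optional status of adjustment, both of which the article states outright.

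**Conclusion.** The point holds in a limited form. The article names an unadjusted one-sided t-test for a non-randomised comparison and leaves adjustment optional. It does not say which result decides, and it omits diagnosis and centre from the optional covariates despite acknowledging that patient mix may change.

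The figures of 16-34% for type I error and 51-34% for power show how sensitive the test is under assumed imbalances. A reader might take them as expected error rates, but the documents contain nothing from which the actual imbalance or its direction could be derived. The sample size itself is not in error. Adjustment would remove measured imbalance only, and a secular trend between the periods would remain whichever model is used.

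**What to change.** State that the primary analysis is a linear regression of the decisional conflict score on period, with a covariate set fixed in advance and entered whatever imbalance is observed. The set should be the plan's own covariates (demographics, performance status, health literacy, hope) plus centre, broad tumour group and baseline quality of life. Report the unadjusted t-test as supportive, and use the same set for the secondary outcomes and the SEM.

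The change is to wording only, since every variable is already collected or known. It costs about 10-12 model degrees of freedom out of 276. The more practical cost is missing data. Health literacy, hope and quality of life come from the first questionnaire, which must be completed in a referral window of about one week. The plan should say how missing covariate values are handled, for example by imputation, so that patients are not dropped from the primary analysis. The report should also acknowledge that a secular trend cannot be adjusted away.
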